**Pilot testing**

Based on the feedback received in the focus groups and the Father Advisory Board, the curriculum will be pretested in a pilot study. Eight sessions will be implemented at one community organization. Each session will be two and a half hours in duration, with a total of 24 contact hours with each father and youth. The research team will develop and finalize research protocols; prepare data collection instruments and methods; train local implementation staff in research and evaluation methods, human subjects’ protections, and data security; and work with the Stakeholder Advisory Team to ensure the cultural compatibility of the intervention, research design and data collection methods.

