**Intervention implementation**

The program will be implemented at collaborating sites in a staggered fashion with recruitment by community sites/agencies that are known and trusted within the Latino community including community-based organizations, extension sites, public schools and churches to enhance recruitment and retention.^36^ Collaborating sites will be reimbursed for their staff time to participate in the project including a parent-trainer who will lead the implementation of the intervention and a site recruitment coordinator. Staff who lead the curriculum sessions are expected to be bilingual Latino fathers themselves and will undergo training regarding parenting practices involved in youth EBRBs and instructional strategies about teaching and learning including group management. Participants will be compensated with cash or gift cards to maximize recruitment and retention.

Twenty (20) parent/youth dyads will attend each of six series of eight weekly sessions. Outcome data will be collected at baseline (prior to session 1), immediate post-intervention (after session 8), and 3 months post-intervention to determine changes in youth EBRBs and weight status, and paternal parenting practices.

The study statistician will use SAS to generate separate randomization schedules for each site. The randomization schedules will be created with randomized blocks of 2, 4, and 6. Within each block, assignments will be balanced between Intervention and Control to ensure approximately equal group size if the complete randomization schedule isn't used.  Random assignments will be printed on colored paper slips, folded 3 times and placed in sequentially numbered opaque envelopes to be distributed to enrolled families by the project coordinator. Eventually, father and youth dyads will be randomized (following block randomization procedures) to intervention or control conditions following completion of outcome data assessments at baseline.

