Youth will participate in 3 24-hour dietary recall interviews^37^ using Nutrition Data System for Research (NDSR) software version 2016^38^ to assess change in intake of low energy dense foods (fruits and vegetables) and high energy dense foods (sugar-sweetened beverages, sweets/salty snacks, and fast foods). Recalls will be collected in-person during the in-person data collection sessions, followed by 2 recalls by phone within the next week. Recalls will be collected on 3 non-consecutive days including 2 weekdays and 1 weekend day. A food amounts booklet will be provided to help adolescents identify quantities consumed. Skin carotenoid levels will also be assessed using reflection spectroscopy with a Veggie Meter as a biomarker of vegetable and fruit intake.^39^ Fathers will complete the Food Behavior Checklist developed and tested for low-income, low literacy adults^40, 41^ to assess intake frequency of fruits, vegetables, sugar sweetened beverages, sweets/salty snacks, and fast food.

Height and weight will be assessed according to established anthropometric methods^42^ using a stadiometer (model: Seca 202, Hanover, MD) and a digital weight scale (model: Tanita BWB-800P Digital Medical Scale, Arlington Heights, IL, USA) to assess whether BMI changes over time among the intervention vs. control group. Three measures of both height (to the nearest 0.1 cm) and weight (to the nearest 0.1 kg) will be collected and averaged. BMI percentiles and z-scores for adolescents will be generated using a SAS program created by the Centers for Disease Control and Prevention.^43^

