For the recalls, adolescents will be asked to report all foods, beverages, and water that they consumed in the last 24 hours. A Food Amounts Booklet will be provided to assist in estimating amounts consumed. All of the recalls will be reviewed by an NDSR certified person (either a graduate student or project coordinator) for data entry error. If there are any data entry errors, these errors will be corrected by the NDSR certified person. After this step, NDSR output files will be produced, and these files will be used in the SAS software to obtain intake data. In the SAS software, intakes will be averaged across the number of recalls, and unreliable recalls will be identified and deleted from the output data files. When all of the cleaning processes is done, NDSR recalls will be used to produce five food groups: fruit intake (servings per day), vegetable intake (servings per day), sugary drink intake (serving per day), sweets/salty snacks intake (serving per day), and fast-food intake (serving per day). The food components that comprised each NDSR food group are shown in Table 3. These five groups' intake data will be compiled into the data sheets of the master data file. Children’s HEI scores will be also calculated by using SAS software with NDSR output files.

**Tab S3.** NDSR food groups and their components.

| **Food groups** | **Food categories** |
| --- | --- |
| Fruit intake | Citrus juice  Fruit juice excluding citrus juice  Citrus fruit  Fruit excluding citrus fruit  Avocado and similar fruit  Fruit-based savory snacks |
| Vegetable intake | Dark-green vegetables  Deep yellow vegetables  Tomato  White potatoes  Other starchy vegetables  Legumes (cooked dry beans)  Other vegetables  Vegetable juice |
| Sugary drink intake | Sweetened soft drinks  Sweetened fruit drinks  Sweetened tea  Sweetened coffee  Sweetened coffee substitute  Sweetened water |

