## **Quality assurance**

Weekly meetings among project staff and primary investigators will be held to assure quality. In these meetings, staff will talk about recruitment, program sessions, facilitators, data collection, and data management and report issues that affect recruitment, implementation, and data collection and management to maintain quality. Community partners will also be asked their feedback on sessions and data collections to assure quality.

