Immigrant communities, due to past trauma in their lives, often have a distrust of government and researchers or research practices.^56^ To address this potential issue, the project team will partner with community agencies that are respected in the community. Research materials and language will be carefully crafted with input from the Father Advisory Board to provide information in a respectful manner. The program will be implemented in conjunction with community collaborators using recruitment methods, which have been successful in the past. Therefore, difficulty recruiting the necessary number of father-early adolescent dyads is not expected. However, a higher attrition rate (20%) may occur. The project team will oversample to account for a higher attrition rate, compensate for time, and work with community agencies to implement the program at convenient times as suggested in a previous study involving programming for Latino immigrant families.^57^ The project team will record reasons for dropouts and address issues to enhance retention.

Accuracy of dietary recall by youth is subject to recall bias based on self-reported intake. However, collection of this information over three days (one day in person) using the NDSR multi-pass approach with visual portion-size estimation aids will minimize this error. In addition, parent input will be sought to answer questions about food products.

Participants will be enrolled from organizations in a single Midwestern state, therefore results may not generalize to Latino families in other regions of the US. However, research on Latino father populations in areas of recent settlement are rare, therefore this information may contribute new knowledge regarding how to prevent overweight or obesity in these rapidly growing but under-researched populations. Sampling bias may also occur because participants may have an interest in the subject matter or a higher level of motivation; therefore, results cannot be generalized to a broader group of parents.

Lastly, contamination may occur given that families being served by community organizations may know each other. Because the time investment in the sessions is significant, and sessions build on each other, parents are unlikely to casually share knowledge with other parents or convey substantive knowledge or skills. This issue can be addressed by discussing the problem with all service providers and asking participants to avoid sharing materials.

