## **Duration of the project**

See figure 2 for the detailed timeline for the project for each site. In summary, after the baseline data collection tasks are completed by all family members who were participating, father and adolescent pairs will be given an envelope containing a random group assignment into either the treatment group or the waitlisted (delayed treatment) control group. The intervention group will be asked to attend the series of educational sessions the week after baseline data collection. The delayed-treatment control group will be asked to attend the series of educational sessions after the three-month data collection session.

**Fig S2.** Diagram of intervention procedures and timeline.

Weeks

| Treatment group | |  | 1 | 2 | 3 | 4 | 5 | 6 | 7 | 8 |  |  |  |  |  |  |  |  |  |  |  |  |  |  |  |  |  |  |  |  |  |  |
| --- | --- | --- | --- | --- | --- | --- | --- | --- | --- | --- | --- | --- | --- | --- | --- | --- | --- | --- | --- | --- | --- | --- | --- | --- | --- | --- | --- | --- | --- | --- | --- | --- |
|  | | D1 | Education sessions | | | | | | | | D2 | 12-week waiting | | | | | | | | | | | | D3 |  | | | | | | | |
| Delayed-treatment control group | |  |  |  |  |  |  |  |  |  |  |  |  |  |  |  |  |  |  |  |  |  |  |  | 1 | 2 | 3 | 4 | 5 | 6 | 7 | 8 |
|  | D1 | 8-week waiting | | | | | | | | D2 | 12-week waiting | | | | | | | | | | | | D3 | Education sessions | | | | | | | |  |

D1 = baseline data collection session

D2 = post data collection session

D3 = follow-up data collection session

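### Nothing in the protocol keeps allocation from those who collect, review or correct the follow-up dietary recalls, which yield five primary behaviours including the powered sugary-drink outcome

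*Protocol*

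**What the plan says.** The protocol describes the relevant steps in separate sections.

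- **Measurement.** Each youth gives three recalls per round: "Recalls will be collected in-person during the in-person data collection sessions, followed by 2 recalls by phone within the next week". Data management turns them into five intake variables: fruit, vegetables, sugary drinks, sweets/salty snacks and fast food. Statistical analysis counts the youth behaviours among the primary outcomes and powers the trial on sugary drinks.
- **Allocation.** Once baseline tasks are finished, "father and adolescent pairs will be given an envelope containing a random group assignment" (Duration of the project). Under Intervention implementation the slips are "placed in sequentially numbered opaque envelopes to be distributed to enrolled families by the project coordinator".
- **Recall review.** "All of the recalls will be reviewed by an NDSR certified person (either a graduate student or project coordinator) for data entry error" (Data management). The same person corrects any errors found, and recalls judged unreliable are later deleted.
- **Files.** The adolescent datasheets of the master file hold intake, height and weight, group assignment and session attendance together (Data management).
- **Meetings.** In weekly meetings "staff will talk about recruitment, program sessions, facilitators, data collection, and data management" (Quality assurance).
- **Training.** Among the preparation tasks under Pilot testing, the team will "train local implementation staff in research and evaluation methods".
- **Recall error.** Expected outcomes of the study acknowledges recall bias from self-report and says that three days of collection "using the NDSR multi-pass approach with visual portion-size estimation aids will minimize this error".

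No section mentions masking, and none names who conducts the recalls or takes the measurements at the post (D2) and follow-up (D3) sessions.

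**The concern.** A multi-pass recall leaves the interviewer some discretion: how far to probe for forgotten drinks, when to accept a portion estimate, when to ask a parent. Correcting a recall and judging it unreliable also involve judgement. If the person doing this knows that a family attended the sessions, slightly less probing for sugary drinks or slightly more for vegetables produces a difference in the hypothesised direction.

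Such a shift is systematic. More dyads, more recall days, covariate adjustment or multiple imputation will not remove it. Who collects outcomes, and what they know, has to be settled before data collection, so it is not a matter to leave to an analysis plan.

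The safeguards that the protocol lists (three days, multiple passes, portion aids) make recalls more complete and less variable. They do not address a difference in handling between the arms.

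**Working it through.** **1. Can those who handle recalls know the arm?** The relevant steps, in order:

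| Step | Who | Knows or could know the arm? |
| --- | --- | --- |
| Envelope handed out after baseline | Project coordinator | Distributes the assignments; family knows from here on |
| D2 and D3 recalls (one in person, two by phone) | Not named | Not excluded |
| Review and correction of recalls | NDSR-certified graduate student or project coordinator | The coordinator role is the one that distributes envelopes |
| Cleaning and compiling | Graduate student | The datasheets carry group and attendance beside intake |
| Weekly meeting | Project staff and primary investigators | Sessions and data collection discussed together |

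The documented overlap is the coordinator role, followed by the shared datasheets. The meeting is weaker evidence, because it is not said that individual families' arms are disclosed there. The training sentence is weaker still.

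**2. The plan's own power figure.** Inputs from Statistical analysis: 120 dyads per arm, 20% attrition, effect 0.5 SD, two-sided alpha 0.05, stated power 90%.

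- Completers per arm: 120 × 0.8 = 96.
- Standard error of the arm difference: √(2/96) = 0.144 SD.
- Power at 0.5 SD: 93.1% (t-test, 190 df) or 93.4% (normal approximation).

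This is a little above the stated 90%, so the discrepancy is conservative and is no part of this point. An observed difference of about 1.973 × 0.144 = 0.285 SD is enough for significance.

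**3. What a handling shift would do.** The documents give no size for such a shift, so the values of b below are assumptions. With no true effect and a shift b in one arm's three-recall mean, the test statistic has noncentrality b/0.144. The rejection rate is the two-sided noncentral t tail with 190 df.

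| Assumed shift b (SD) | Noncentrality | Two-sided rejection rate |
| --- | --- | --- |
| 0 | 0 | 5.0% |
| 0.05 | 0.35 | 6.4% |
| 0.10 | 0.69 | 10.6% |
| 0.15 | 1.04 | 17.9% |
| 0.20 | 1.39 | 28.1% |

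A shift of 0.10 SD is one fifth of the 0.5 SD target effect.

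**4. Masking the phone recalls only.** Suppose the shift is the same on each recall and masking removes it entirely on the two phone calls. One third then remains: 0.10 SD becomes 0.033 SD (rejection 5.6%), and 0.20 SD becomes 0.067 SD (7.5%). This is a best case for that measure.

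**The case against.** The strongest reply is that the protocol omits a statement about masking but does not plan to unmask anyone. A reader might infer from the training sentence that session staff will interview and measure the youth. The text does not support that: the sentence sits among preparation tasks and assigns no outcome collection. The roles that are described lean somewhat the other way. Session leaders are to be trained in parenting practices and teaching, while students do data entry and cleaning. That reply stands, although described roles that happen to differ are not a rule of separation.

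A reader might also infer that handing out the envelope at the end of baseline is a fault. It is not. It protects the in-person baseline assessment, and a delayed-treatment design cannot hide the arm from families. The exposure is at D2 and D3. Whether the two baseline phone recalls come before the envelope is not clear from the text.

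Nor does the concern apply equally to every primary outcome. Height and weight are each the mean of three instrument readings, and activity and screen time are questionnaire items, so assessor influence there is smaller.

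Finally, families know their arm and may mention it, so masked interviewers would not remove self-report bias. That is true, but assessor handling is a separate source of bias, and this one can be avoided.

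**Conclusion.** The point holds as an unprotected step, not as a stated plan to use unmasked assessors. If the protocol is followed as written, those who collect, review or correct the D2 and D3 recalls may know the arm. At least one role that may correct recalls also handles allocation.

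The outcome most exposed is the one the trial is powered on. The size is unknown: over assumed shifts of 0.05 to 0.20 SD, the false-positive rate runs from 6.4% to 28.1% instead of 5%. These figures rest on 96 completers per arm, a two-sample comparison without covariates, no true effect, and a shift confined to one arm. They show sensitivity and do not estimate what will happen. The change is a worthwhile, low-cost improvement.

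**What to change.** Add the following.

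- **Measurement:** D2 and D3 recalls (at minimum the two phone recalls) and, where feasible, height and weight are taken by existing data staff who neither deliver sessions nor handle envelopes, working from ID-only lists. Families are asked at each contact not to say which group they are in.
- **Data management:** recalls are reviewed, corrected and judged unreliable by the NDSR-certified graduate student rather than the coordinator, on files without group or attendance. Those two fields are kept apart and merged only after recall cleaning is complete. This matters because a graduate student also compiles the master file.
- **Quality assurance:** session and attendance matters are taken in a part of the weekly meeting that the data collectors do not attend.

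The cost is protocol wording, a split of roles and some scheduling effort. It assumes that enough data staff are available to separate the roles, which the protocol does not confirm. Some families will still reveal their arm, and participants' own reporting bias is untouched.

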**Intervention implementation**

The program will be implemented at collaborating sites in a staggered fashion with recruitment by community sites/agencies that are known and trusted within the Latino community including community-based organizations, extension sites, public schools and churches to enhance recruitment and retention.^36^ Collaborating sites will be reimbursed for their staff time to participate in the project including a parent-trainer who will lead the implementation of the intervention and a site recruitment coordinator. Staff who lead the curriculum sessions are expected to be bilingual Latino fathers themselves and will undergo training regarding parenting practices involved in youth EBRBs and instructional strategies about teaching and learning including group management. Participants will be compensated with cash or gift cards to maximize recruitment and retention.

Twenty (20) parent/youth dyads will attend each of six series of eight weekly sessions. Outcome data will be collected at baseline (prior to session 1), immediate post-intervention (after session 8), and 3 months post-intervention to determine changes in youth EBRBs and weight status, and paternal parenting practices.

The study statistician will use SAS to generate separate randomization schedules for each site. The randomization schedules will be created with randomized blocks of 2, 4, and 6. Within each block, assignments will be balanced between Intervention and Control to ensure approximately equal group size if the complete randomization schedule isn't used.  Random assignments will be printed on colored paper slips, folded 3 times and placed in sequentially numbered opaque envelopes to be distributed to enrolled families by the project coordinator. Eventually, father and youth dyads will be randomized (following block randomization procedures) to intervention or control conditions following completion of outcome data assessments at baseline.

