## **Statistical analysis**

During the planning year, focus group interviews will be audio recorded and transcribed verbatim. A codebook will be developed, and transcripts will be coded by two independent project team members. A software program (NVivo v.12, QSR International (Americas) Inc., Burlington, MA) will be used to organize and enable analysis of coded transcripts. Facilitators and barriers to youth EBRBs and parenting practices will be identified using content analysis procedures based on recurring themes.^55^

Father and youth dyads assigned to the intervention condition (n = 120 dyads) will participate in the program immediately, while father and youth dyads assigned to the delayed-control condition (n = 120 dyads) will participate in the prevention program after the 3 months post intervention data collection session. This will allow detection of an effect size of 0.5 standard deviations in sugared-sweetened beverages (SSBs) 24-hr dietary recall with 90% power accounting for a 20% attrition rate (at 3 months post intervention follow-up).

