Demographic characteristics of intervention and control group participants will be compared at baseline using t-tests for continuous variables and chi-square tests for categorical variables to assess whether participant characteristics were equivalent between groups. Adjustments for differences between groups will be done as needed. The primary outcomes, youth EBRBs, BMI-for-age percentile, and BMIz scores, will be evaluated by a multiple regression model (SAS software, SAS Institute Inc., Cary, NC) to test the null hypothesis that immediate post-intervention and 3-month post intervention outcomes are the same in the intervention and control groups. Baseline outcomes, covariates to adjust for baseline differences, potential confounders and site effect will be included in the regression model, to generate least squares adjusted mean changes, to generate a model comparing the intervention to control group. The secondary outcomes, self-reported parenting practices, will be evaluated by ANCOVA models to test the null hypotheses for each of the identified parenting behavior scale scores. Covariates to adjust for baseline differences, potential confounders and site effect will be included in the models to generate least squares adjusted mean changes for each group. A two-tailed significance level (alpha) of 0.05 will indicate statistically significant differences. The response rate expectation at 3 months post-intervention is 80% (based on 20% loss-to-follow up). This expected loss-to-follow up was accounted for in the power analysis for the primary outcome, which is based on 120 families per group. Multi-imputation of missing data is planned for the primary study outcome EBRBs. Chi-square tests and two-sample t-tests will be used to compare baseline characteristics between study completers and those lost to follow up to assess the potential for intervention effect bias due to study dropout. Secondary parenting outcome analyses will only include subjects with parenting practices scales data at the indicated data collection times for each analysis.

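### Group delivery in one arm only is allowed for neither in the 90% power statement nor in the primary regression; both hold as written only if dyads in the same series stay nearly independent

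*Protocol*

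**What the plan says.** Under Intervention implementation: "Twenty (20) parent/youth dyads will attend each of six series of eight weekly sessions". The same section has the statistician prepare a separate randomisation schedule for each site and has a site-based parent-trainer lead delivery. The Project summary gives 40 dyads at each of six sites, randomised as dyads.

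Under Statistical analysis: "Father and youth dyads assigned to the intervention condition (n = 120 dyads) will participate in the program immediately", with the same number in the delayed-control arm. Duration of the project places the controls' sessions after the three-month data collection, so they are ungrouped at every outcome visit.

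The power claim is: "This will allow detection of an effect size of 0.5 standard deviations in sugared-sweetened beverages (SSBs) 24-hr dietary recall with 90% power". The only allowance named is 20% attrition. For the primary outcomes: "Baseline outcomes, covariates to adjust for baseline differences, potential confounders and site effect will be included in the regression model". For significance: "A two-tailed significance level (alpha) of 0.05 will indicate statistically significant differences". There is no ICC, design effect, series term or site-by-arm term, and the protocol does not say whether site is fixed or random.

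That each site runs one intervention series is an inference, not a statement: 40 dyads split 1:1 gives 20 per site, and 6 × 20 = 120.

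**The concern.** Dyads in a series share a trainer, eight weeks of group sessions and each other's company. If this makes their outcomes alike, the intervention arm carries less information than 120 independent dyads, while the control arm does not change. This is a partially nested design.

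The site effect looks like protection but is not enough. It removes differences common to both arms at a site. A series effect exists in one arm only, so it acts as a site-by-arm difference and passes straight into the treatment contrast. The regression then uses too small a standard error. At stake are the size of the primary tests, on which the efficacy claim rests, and the stated power.

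**Working it through.** **Inputs.** From the protocol: two-sided alpha 0.05; effect 0.5 SD; 120 dyads per arm; 20% loss, so 120 × 0.8 = 96 completers per arm; six series, so 96/6 = 16 completers each. Assumed: ICC from 0 to 0.10 in the intervention arm, total variance 1 in both arms, equal series sizes.

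**The plan's own figure, independent dyads.**
- Needed per arm: 2 × (1.960 + 1.282)² / 0.5² = 84.06, so 85 evaluable, and 85/0.8 = 106.25, so 107 enrolled.
- The plan enrols 120. With 96 completers the standard error is √(2/96) = 0.1443 and power is Φ(0.5/0.1443 − 1.960) = Φ(1.504) = 93.4%.

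So the stated 90% is met with some reserve if dyads are independent. The protocol does not explain the reserve.

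**With clustering in the intervention arm.**
- Variance of the arm difference: [1 + (16 − 1) × ICC]/96 + 1/96 = (2 + 15 × ICC)/96.
- Inflation over 2/96: 1 + 7.5 × ICC.
- True type I error of the regression as written: 2 × [1 − Φ(1.960/√inflation)].
- Power of a test that uses the correct variance: Φ(0.5/√variance − 1.960).

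| ICC | Inflation | Type I error as written | Correct SE | Power, normal approximation |
|---|---|---|---|---|
| 0 | 1.000 | 5.0% | 0.1443 | 93.4% |
| 0.01 | 1.075 | 5.9% | 0.1497 | 91.6% |
| 0.02 | 1.150 | 6.8% | 0.1548 | 89.8% |
| 0.05 | 1.375 | 9.5% | 0.1693 | 84.0% |
| 0.10 | 1.750 | 13.8% | 0.1909 | 74.5% |

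Setting power to 90% requires (2 + 15 × ICC)/96 = (0.5/3.2415)², which gives ICC = 0.019.

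**Does the site term help?** A regression with fixed site effects and one series per site was simulated (20,000 runs per ICC). Type I error was 5.1%, 6.9%, 9.5% and 13.7% at ICC 0, 0.02, 0.05 and 0.10, in line with the formula. The uncorrected test still detected 0.5 SD about 90% of the time at ICC 0.05, but as a test of size 9.5%.

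**Degrees of freedom.** The normal approximation flatters a design with six series. If site is fixed and each site has one series, the arm effect is the mean of six within-site differences, with 6 − 1 = 5 df. Noncentral t power with the standard errors above is then about 79% at ICC 0, 76% at 0.01, 73% at 0.02 and 66% at 0.05, before baseline adjustment.

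**The case against.** Several points on the other side are sound.

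- **The stated 90% is not shown to be false.** A reader might infer that it fails as soon as series members are at all alike. The documents do not support that: 120 exceeds the 107 needed, and 90% survives to an ICC of about 0.02 by the normal approximation. The excess could even be an unstated allowance.
- **No ICC is documented.** Nothing in the protocol shows which value is usual for youth dietary recalls. It cannot be said as fact that the p-values will be too small, only that they would be at any positive ICC.
- **Baseline adjustment is planned and helps power.** Suppose a baseline correlation of 0.5 and ICC 0.05. If the adjustment shrinks all variance by 1 − 0.5² = 0.75, power is Φ(0.5/√(0.75 × 2.75/96) − 1.960) = 93%. If it cannot touch the series component, which arises after baseline, the variance is 0.05/6 + 0.70/96 + 0.75/96 = 0.0234 and power is 90%. Neither case repairs the type I error.
- **The inferential target matters.** For the average effect in these six series as delivered, an analysis without a random series effect is defensible, and the protocol already limits generalisation. The inflated type I error applies to claims about the programme run elsewhere with other series. The stated purpose, evaluating the efficacy of a curriculum, points towards such claims.
- **Model detail may sit in an analysis plan not at hand.** That covers df methods and random structure. It does not cover the unconditional power sentence or the model as written, both of which the protocol fixes.
- **The protocol plans adjusted mean changes and p-values and does not mention confidence intervals.** The same standard errors underlie both.

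It is also tempting to use a two-sample Satterthwaite calculation without site effects (about 17, 15, 12 and 10 df at ICC 0.01, 0.02, 0.05 and 0.10), which gives 88.2%, 85.6%, 77.5% and 65.4% power. Those figures do not belong to a model with fixed site, which has about 5 df.

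**Conclusion.** The defect is real but conditional. The design clusters one arm, the power statement and the regression ignore this, and a site effect common to both arms does not cure it. For inference beyond these six series, the regression as written has a true type I error of about 6%, 7%, 9.5% and 14% at ICC 0.01, 0.02, 0.05 and 0.10. The stated 90% power holds up to an ICC of about 0.02 by the normal approximation, and falls to 84% at 0.05 and 74% at 0.10 before baseline adjustment.

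These figures rest on an assumed ICC range, 16 completers in each of six series, and one series per site. The spare sample size cushions power only; it does nothing for the type I error. A reader might also conclude that a mixed model must replace the primary regression. The documents do not force that, because with so few series it is a trade-off between validity and power.

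**What to change.** 1. Restate the power sentence as 90% assuming independent dyads, and show power over ICC 0.01 to 0.05. State that the ICC is assumed.
2. Prespecify a partially nested analysis: baseline value, arm and site, a random series effect for intervention dyads only, and small-sample degrees of freedom. Make it at least a sensitivity analysis, and say that a positive primary result will be read against it.
3. State whether site is fixed or random and whether each site runs one series. Derive the degrees of freedom and power for the model actually chosen.

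None of this needs extra enrolment, provided the power is restated and not defended at 90% for every ICC. Holding 90% at ICC 0.05 by the normal approximation, with 16 completers per series, would take (2 + 15 × 0.05) × (3.2415/0.5)² = 115.6, so 116 evaluable and 116/0.8 = 145 enrolled per arm.

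The cost is wider intervals (√1.375 = 1.17, so 17% wider at ICC 0.05 on the normal scale) and less favourable stated power. If the fixed-site version with about 5 df were made the sole primary analysis, unadjusted power would be about 79% even with no clustering. This is why a sensitivity role is a reasonable minimum.
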